### Plans to promote participant retention and complete follow-up {18b}

During participant recruitment, the purpose and importance of the trial will be explained via the study team and PICF. The participant has the right to withdraw from the trial at any time and for any reason without prejudice to her medical care and routine treatment by the treating team or at the institution. If a participant withdraws from the trial before concluding the study and since the data will be recorded anonymously, an intention-to-treat analysis will be performed for such patients’ data. If a patient is withdrawing their consent during the conduction of the trial and unwilling to consent for utilising already collected data and if these specific data can be retrieved, the investigator will delete the data accordingly.

### Data management {19}

Data will be collected on a paper questionnaire. The collected information will remain anonymous; participants will be allocated a participant number for de-identification purposes. The hard copy questionnaires will be scanned to create an electronic copy and the data transferred to a MS Excel database for assessment; data will be kept securely within the organisation’s network. All data will be stored with the principal investigator in a Goulburn Valley Health password-protected computer for a period of 5 years. Any hard copies of the data will be shredded/destroyed and disposed of in Goulburn Valley Health’s confidential paper/document collection bins and all soft copies of the data will be permanently deleted from the computer once the data storage time is over or at the conclusion of the study.

### Confidentiality {27}

Study investigators will ensure that the participants’ anonymity is maintained. Participant numbers are allocated for de-identification purposes; no identifiable information will be used but an aggregated data for dissemination. Prior to study participation, patients are informed that except for the study investigators, nobody will have access to the dataset unless there is an institutional or regulatory requirement. Hard copies of data are shredded/destroyed in confidential paper/document collection bins as soon as soft copies are made during the study. Soft copies are stored securely with the principal investigator on an organisational password-protected computer/network and will be destroyed 5 years after the study’s conclusion.

### Plans for collection, laboratory evaluation and storage of biological specimens for genetic or molecular analysis in this trial/future use {33}

No biological specimens will be collected for future genetic or molecular analysis.

## Statistical methods

### Statistical methods for primary and secondary outcomes {20a}

Baseline characteristics of participants including demographic characteristics, morbidity information with severity, current medication/management and satisfaction towards the current management will be compared using the *t*-test or and *χ*^2^ tests for categorical variables to assess the success of the randomisation. Summary statistics will be presented for all three groups’ infection information. BMI will be calculated using the weight and height of the participants. If required, the analysis will be performed following the ‘intention-to-treat’ analysis method. Primary and secondary outcomes will be compared using ANOVA. Where appropriate, logistic regression analyses will be used to compare the outcomes separately for interventions versus the control group. All data will be entered in MS Excel, and all statistical analyses will be performed using the STATA 11.0 statistical package.

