
### Objectives {7}

#### Hypothesis

H_1_: In a blinded randomised controlled clinical trial, using either chlorhexidine or povidone iodine for vaginal irrigation prior to CS will reduce post-operative infection outcomes by 50% when compared to no vaginal irrigation.

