#### Aims

The aims are to introduce uniform use of vaginal antiseptic wash immediately prior to CS and to determine the best antiseptic wash material in reducing post-operative infections or complications.

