### Outcomes {12}

#### Primary outcome

The primary outcome is endometritis: defined as tympanic temperature > 38 °C with uterine tenderness and/or foul-smelling vaginal discharge within 28 days of post-CS.

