### Sample size {14}

We assume that the interventions will improve the rate of infection including post-operative infective complications (within 28 days post-CS) by 50% compared to the control. Thus, for sample size estimation in this study, we set *P*_1_ = 8% (as per overall prevalence of post-CS infection range 3–15%), *P*_2_ = 4%, significance level = 5% and the study power = 80%.

Therefore,
$$ n\ge {\left(\frac{Z_{\alpha }+{Z}_{\beta }}{\mathrm{ES}}\right)}^2 $$$$ \mathrm{ES}=\frac{P_1-{P}_2}{\sqrt{P_1\left(1-{P}_1\right)}} $$

*n* ≥ 361

Here, *Z*_*α*_ = 1.96, *Z*_*β*_ = 0.84, *P*_1_ = 0.08, *P*_2_ = 0.04 and *P*_1_ − *P*_2_ = 0.04.

Considering 10% dropout, the study will require recruiting approximately 396 participants for all the groups (*n* = 132 in each group) over a period of 16 months to adequately test the assumption.

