### Methods for additional analyses (e.g. subgroup analyses) {20b}

No additional analyses are planned.

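### ANOVA is named for yes/no infection outcomes and gives no relative effect, and no planned analysis compares chlorhexidine with povidone iodine although finding the best antiseptic is a stated aim

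*Protocol article*

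**What the plan says.** All references are to the protocol article.

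- **Outcomes {12}.** The primary outcome is a yes/no event: "The primary outcome is endometritis: defined as tympanic temperature > 38 °C", together with local signs, within 28 days. The three secondary outcomes (fever, wound infection, readmission with infection) are also yes/no events.
- **Statistical methods {20a}.** "Primary and secondary outcomes will be compared using ANOVA". The next sentence reads: "Where appropriate, logistic regression analyses will be used to compare the outcomes separately for interventions versus the control group". The same section assigns chi-square tests to categorical baseline variables.
- **Hypothesis.** "using either chlorhexidine or povidone iodine for vaginal irrigation prior to CS will reduce" post-operative infection outcomes by half compared with no irrigation.
- **Aims.** One of the two aims is "to determine the best antiseptic wash material in reducing post-operative infections or complications". The fourth objective and the Discussion repeat it.
- **Additional analyses {20b}.** "No additional analyses are planned".
- **Sample size {14}.** Control 8%, intervention 4%, significance level 5%, and 132 women per group. The 8% is described "as per overall prevalence of post-CS infection range 3–15"%, so it is a rate for infection overall and not for endometritis.

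**The concern.** ANOVA compares means under a common variance. For a yes/no outcome the arm mean is a proportion p with variance p(1−p), so the variances differ whenever the rates differ. More to the point, ANOVA delivers a global test and mean differences, while the hypothesis is a halving of risk. The method that does give a relative measure is left conditional.

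The second problem is a mismatch between aim and analysis. A global test cannot say which antiseptic is better. Two comparisons against a shared control do not put an estimate or an interval on the difference between the antiseptics. As written, the trial could finish without any planned figure behind a recommendation of one product over the other.

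The third is the wording of the hypothesis. If success on either antiseptic counts and each is tested at 5%, the overall error rate exceeds the 5% used in the sample size section.

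**Working it through.** **Inputs.** From Sample size {14}: p = 0.08 (control), 0.04 (each antiseptic), alpha 5%, 132 per arm. With the stated 10% dropout, 132 × 0.9 ≈ 119 per arm. The antiseptic-versus-antiseptic rates (4% v 2%) and any rates below 8/4/4% are assumptions, because the article gives none.

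**The plan's own figure.** ES = 0.04/√(0.08 × 0.92); ((1.96 + 0.84)/ES)² = 360.64, rounded up to 361. The stated n reproduces.

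**1. Does ANOVA spoil the global test?** No. For 0/1 data with N women in three arms, F is a one-to-one function of the Pearson statistic X²:

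F = (X²/2) / ((N − X²)/(N − 3))

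At N = 396 the 5% critical F (2 and 393 df) is 3.0187, which corresponds to X² = 5.9914. The chi-square critical value is 5.9915. In 400,000 simulated trials per scenario the two tests never disagreed. Type I error at 132 per arm was 4.7% to 5.0% for common rates of 3%, 4%, 8% and 15%. At 8/4/4% both rejected in 29.0%.

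**2. Pooled-variance intervals, if used.** Variances: 0.08 × 0.92 = 0.0736; 0.04 × 0.96 = 0.0384. Pooled: (0.0736 + 0.0384 + 0.0384)/3 = 0.0501. At 132 per arm:

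| Contrast | True SE | ANOVA SE | Ratio | 95% CI coverage, ANOVA (unpooled Wald) |
|---|---|---|---|---|
| Control v antiseptic | √(0.1120/132) = 0.0291 | √(2 × 0.0501/132) = 0.0276 | 0.95 | 93.7% (94.7%) |
| Antiseptic v antiseptic | √(0.0768/132) = 0.0241 | 0.0276 | 1.14 | 97.6% (95.5%) |

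**3. Which contrasts are planned?**

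| Question in the aims, objectives or hypothesis | Planned analysis |
|---|---|
| Do rates differ among the three groups? | ANOVA (global) |
| Does an antiseptic halve the rate against control? | Logistic regression, conditional |
| Which antiseptic is better? | None named |

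**4. What could a head-to-head comparison show?** Power for 4% v 2%, two-sided 5%, is 15.6% at 132 per arm and 14.5% at 119. About 1,141 per arm would be needed for 80%. With 4% in both arms the 95% half-width at 132 per arm is 1.96 × 0.0241 = 4.7 percentage points.

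**5. Two tests against control, success on either.** Simulated two-sided false-positive rate with no preceding global test, 8% in every arm: 9.7% at 119 per arm, and 9.0% to 9.8% at 132 depending on the variance form of the z test. At a common 3% it is about 8%. These rates count a difference in either direction; apparent benefit alone is about half. If the three-arm test must reject first, the rate is below 5% in every case run.

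**6. Empty arms.** P(at least one arm with no events) = 1 − ∏(1 − (1 − p)^n). At 119 per arm this is 1.6% at 8/4/4%. At assumed rates of 3/1.5/1.5% it is 32%, and at 2/1/1% it is 56%.

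**The case against.** The strongest reply is that ANOVA changes no decision here, and step 1 confirms it. A reader might infer that naming ANOVA invalidates the primary test or makes the trial's confidence intervals wrong. The article does not support that. Unequal variances do not arise when the rates are equal, and nowhere does the article promise ANOVA-based intervals. The comparison with control is assigned to logistic regression, which does not use the ANOVA error term.

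The logistic model also gives a relative measure. At the planned rates the odds ratio is (0.04/0.96)/(0.08/0.92) = 0.48, close to the risk ratio of 0.50. That stands, but only where the model is judged appropriate, and only against control.

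Three further readings go beyond the text:

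- **Unadjusted models.** The article is silent on covariates, and its fifth objective concerns factors that influence the outcomes.
- **Empty arms are likely.** At the plan's own rates the chance is about 1.6%. The high figures rest on assumed rates.
- **The 5% level is certainly broken.** The two sentences in {20a} can be read as a global test followed by contrasts, or as one pooled contrast. The 9–10% arises only if there are two tests with no preceding condition.

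It can also be said that post-hoc pairs belong in an analysis plan and that {20b} concerns subgroup analyses. This has some force. But the article does specify its pairwise analysis, confines it to "logistic regression analyses will be used to compare the outcomes separately for interventions versus the control group", and then rules out anything further. That conflicts with a stated aim and is more than an omitted detail.

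**Conclusion.** The point holds in a limited form, as a correction of analysis wording and not a failure of validity.

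- **Established from the text:** ANOVA is named for outcomes that are all yes/no, the method suited to them is only conditional, and nothing compares chlorhexidine with povidone iodine. The missing contrast is the weightier part.
- **Modest and conditional:** standard errors about 5% too small against control and 14% too large between antiseptics, if pooled-variance intervals are reported and the rates are 8/4/4%.
- **Conditional on reading:** a two-sided false-positive rate of about 9–10% (null 8%), if the two comparisons with control carry no preceding test and either counts as success.

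Adding the head-to-head contrast closes the gap between aim and analysis. It does not make that comparison informative at this size, so the trial can describe the difference between antiseptics but is unlikely to settle it.

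**What to change.** Rewrite the outcome sentences in Statistical methods {20a}:

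1. Replace ANOVA with a three-arm chi-square test at 5%, using the exact version (Fisher-Freeman-Halton) when expected counts fall below 5.
2. Only if that test rejects, test each antiseptic against control at 5%. With three arms this holds the family-wise error at 5% without splitting alpha.
3. Report risk ratios and risk differences with score-based 95% confidence intervals for all three pairs, including chlorhexidine versus povidone iodine.
4. Label the head-to-head result as estimation only, with no test, and word the aim of finding the best antiseptic to match.
5. Use Firth or exact logistic regression if an arm has no events.

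The cost is wording, with no change to conduct or data collection; it should be settled before any analysis by arm. The statistical downside is that a single pairwise p < 0.05 without a significant three-arm test can no longer be claimed. At 8/4/4% and 132 per arm, the chance of claiming at least one antiseptic effective falls from about 41% to about 29%.

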### Trial design {8}

This will be a single-centre, three-arm, single-blind, randomised controlled trial. A total of 396 eligible patients will be randomised in a 1:1:1 ratio to receive pre-operative vaginal cleansing with 1% povidone iodine or chlorhexidine or no toileting (control) immediately prior to CS.

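### The 80% power claim fails on the plan's own 8% and 4% rates: the planned comparisons have about 26–29%, and both antiseptics combined against control only about 36–40%

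*Protocol article*

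**What the plan says.** All references are to the protocol article.

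- **Hypothesis:** "using either chlorhexidine or povidone iodine for vaginal irrigation prior to CS will reduce post-operative infection outcomes by 50" per cent compared with no irrigation.
- **Sample size {14}:** "We assume that the interventions will improve the rate of infection including post-operative infective complications" by half. The control rate is 8%, justified "as per overall prevalence of post-CS infection range 3–15" per cent. The remaining inputs are an intervention rate of "4%, significance level = 5% and the study power = 80" per cent. The formula gives 361, and then: "Considering 10% dropout, the study will require recruiting approximately 396 participants for all the groups", that is, 132 per group.
- **Trial design {8}:** "A total of 396 eligible patients will be randomised in a 1:1:1 ratio". The Abstract and Discussion give 375 (125 per group) instead.
- **Statistical methods {20a}:** primary and secondary outcomes are compared by ANOVA. Where appropriate, "logistic regression analyses will be used to compare the outcomes separately for interventions versus the control group".
- **Additional analyses {20b}:** "No additional analyses are planned".
- **Aims and Objectives:** these also ask for a comparison of the three groups and for the best antiseptic.
- **Primary outcome {12}:** endometritis within 28 days.

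**The concern.** The hypothesis and the sizing speak of one halving of risk from antiseptic cleansing. The tests named in {20a} either ask whether three rates differ in any way or, on the natural reading, set one antiseptic arm at a time against control. Neither is the direct test of antiseptic against none, and the 80% is attached to neither. It comes from a single calculation whose result is used as the total for all three arms.

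Readers will rely on the 80% when they interpret a null result. If the real power is nearer one in four, a non-significant comparison says little about whether cleansing works. A secondary question is whether the same women could answer the general question better through a combined contrast.

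**Working it through.** **1. The plan's own figure.** ES = 0.04/√(0.08 × 0.92) = 0.1474, and n = ((1.96 + 0.84)/0.1474)² = 360.6, so 361. This reproduces. Dropout: 361 × 1.1 = 397 and 361/0.9 = 401, both close to 396. The formula has the variance of one group only, so it is a one-sample formula, yet its result is spread over three arms. The usual two-sample calculation for 8% against 4% (two-sided 5%, 80% power) gives 553 per arm.

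**2. Inputs for the power check.** Control 8%, each antiseptic 4%. Two-sided 5%, which is implied by the 1.96. Per arm: 132 as randomised, or 132 × 0.9 ≈ 119 after the stated dropout. The 125 per group in the Abstract lies between these.

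**3. Formula.** Power ≈ Φ[((p₁ − p₂) − 1.96 s₀)/s₁], where s₀ is the standard error under the pooled rate and s₁ the standard error under the separate rates.

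- One antiseptic against control, 132 v 132: pooled rate 0.06; s₀ = √(0.06 × 0.94 × 2/132) = 0.0292; s₁ = √((0.0736 + 0.0384)/132) = 0.0291. Then (0.04 − 0.0573)/0.0291 = −0.59, so power is about 0.28. Exact enumeration of the chi-square test gives 0.272.
- Both antiseptics against control, 132 v 264: pooled rate 0.0533; s₀ = 0.0240; s₁ = √(0.0736/132 + 0.0384/264) = 0.0265. Then (0.04 − 0.0469)/0.0265 = −0.26, so power is about 0.40. Exact: 0.397.

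**4. Results at 8/4/4%** (two-group tests by exact enumeration; the rest by simulation of 400,000 trials).

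| Test | 119 per arm | 132 per arm |
|---|---|---|
| One antiseptic v control, 5% | 26% | 27% |
| Three-group test | 26% | 29% |
| Either antiseptic, 2.5% each | 26% | 29% |
| Both antiseptics combined v control | 36% | 40% |

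The combined contrast gains about 10–12 points. Relative to it, the three-group test loses 27–28% of the power (1 − 0.289/0.397 = 0.27) and one pairwise test 29–32% (1 − 0.272/0.397 = 0.31).

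**5. If the agents differ (132 per arm).**

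| Control / agent A / agent B | Combined | Three-group |
|---|---|---|
| 8/4/6% | 23% | 21% |
| 8/3/6% | 31% | 33% |
| 8/4/8% | 13% | 25% |

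**6. If the combined test gated the agent comparisons (132 per arm).** Power for a given antiseptic would fall from 27% to 24% at 8/4/4%, and from 27% to 11% if only that agent works.

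**7. What 80% would take at 8% v 4%.** The combined contrast needs 396 controls and 792 antiseptic patients, 1,188 in all. Each pairwise comparison needs 553 per arm, or 3 × 553 = 1,659 in all.

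**The case against.** A reader might infer that the plan assumes the two antiseptics are equal, and so discards about a third of its power by not making a combined test primary. The documents do not support that.

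- One planning rate sets a target effect; it is not a claim of equality. The Aims and Objectives ask which antiseptic is best, and the Background cites evidence that ranks 1% povidone iodine first. Three-group and agent-specific comparisons serve those aims, and a combined contrast cannot.
- A loss of a third is too strong. It is 27–32%, depending on the test. If significance of either agent at an unadjusted 5% counts as success, nothing is lost (41% against 40% at 132 per arm), although the family-wise error is then about 9–10%. The protocol states no such rule.
- The logistic regression sentence is ambiguous. It could mean the interventions together against control, with each outcome analysed separately. That reading is less natural, but it cannot be excluded.
- Item {20b} concerns subgroup and similar analyses. It does not forbid a contrast within the {20a} model, and an analysis plan that is not shown may specify one.

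All four points stand, and they rule out a gating combined test as a correction of an error. They do not rescue the 80%: every reading of {20a} leaves power at about 41% or less.

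**Conclusion.** The 80% power statement is wrong on the protocol's own inputs. The comparisons that {20a} most naturally describes have about 26–29% power, and the contrast closest to the hypothesis about 36–40%. This rests on 8% against 4%, a two-sided 5% level and 119–132 women per arm. It does not depend on how the ambiguous sentence is read.

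The 8% is an overall post-caesarean infection rate, while the primary outcome is endometritis. None of these figures is therefore an established power for the primary outcome. They show only what the trial's planning rates deliver.

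The lack of a clearly named combined contrast is a smaller matter. Adding one is worthwhile for the general question, but the gain depends on similar effects: it almost disappears at 8/4/6% and reverses at 8/3/6%. Combining the arms does not repair the sample size.

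**What to change.** 1. In Sample size {14}, replace the 80% claim with the power delivered at 8% against 4%: about 26–29% for the planned agent-specific and three-group comparisons, and about 36–40% for the combined contrast. State there that 8% is an overall infection rate, and that power for endometritis needs its own assumed rate.
2. In Statistical methods {20a}, say which groups the logistic regression compares. Prespecify both antiseptic arms combined against no cleansing as the test of the general question of antiseptic against none. Report it alongside the agent-specific and three-group comparisons, with none of them conditional on it.
3. State the limitation: if only one agent works, the combined contrast has about 13% power against 25% for the three-group test.

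The cost is wording only, with no change to recruitment, data collection or treatment. The price is an open statement that the trial is far below 80% power. Reaching 80% would need a much larger trial, which is a separate decision.

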### Interim analyses {21b}

No interim analyses are planned. It is unlikely that the trial will be stopped prematurely; however, the study can be temporarily suspended or prematurely discontinued for reasons such as safety and ethical concerns. The sponsoring organisation, relevant ethics committee and the research governance officer of the participating organisation authorities will be informed promptly of the decision including the reasons for such decision.

### Methods for additional analyses (e.g. subgroup analyses) {20b}

No additional analyses are planned.

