## Introduction

### Background and rationale {6a}

Caesarean section (CS) is one of the methods of operative delivery in childbirth, and its rate has increased internationally over the last 3 decades for various reasons. According to the Australian Institute of Health and Welfare, the CS rate in Australia was 34% in 2016 [1]. Similar to any other surgical procedure, CS has morbidity in the form of infections, which include endometritis in addition to surgical site infection (SSI). This is a matter of concern as it has been reported that CS can have ten times higher risk of infections than that of vaginal delivery [2]. Furthermore, higher rates of infection have been identified in women with ruptured membranes and in women who undergo a CS in labour [3]. Such infections cause additional burden not only to the mother herself, but also to the newborn and her family as a whole. It also increases the risk of hospital readmissions and cost to health care systems across the world [4]. Olsen et al. demonstrated that wound infection and endometritis may incur an additional cost of US $4200 and US $4500 to the health systems, respectively [5]. Evidence favours the use of prophylactic antibiotics for CS to reduce post-operative infections by 60–70%, as well as the cost and duration of hospitalisation [6–8]. However, there are debates regarding single versus multiple doses, routes and timing of antibiotic use, type of antibiotics and duration. To reduce the rate of post-CS infections further, different antiseptics have been practised inconsistently for skin preparation and vaginal toileting. It has been demonstrated that vaginal preparation with povidone iodine or chlorhexidine solution compared to saline or not cleansing immediately before CS probably reduces the risk of post-CS infection [3]. However, a Cochrane review suggests no clear evidence favouring the use of chlorhexidine solution before surgery over other washing products to prevent SSI [9], while another Cochrane review reported that use of either chlorhexidine or povidone iodine before CS did not make any or might make little difference to the SSI or endometritis [2]. On the other hand, the World Health Organization (WHO) recommends the use of povidone iodine for vaginal cleansing immediately before CS to reduce maternal infection morbidities [10]. This recommendation is further emphasised in a recent systematic review and network meta-analysis by Roeckner et al. which reported that the use of 1% povidone iodine for pre-surgical vaginal irrigation among women who underwent CS had the most beneficial outcomes in the reduction of fever, wound infections and endometritis [11]. Despite the above measures, SSI incidence ranges from 3 to 15% [12], perhaps due to the variability of practices and individual preferences to one antiseptic agent over the other. Given the current limited data, it is imperative to identify the best evidence-based practice for uniform use of antiseptic agents for vaginal toileting to reduce post-CS infections or complications and to standardise their practice in a regional Australian hospital for enhanced recovery after caesarean delivery (ERAs).

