#### Objectives

The following are the objectives:
To determine the number of post-CS infections among women that will undergo pre-operative vaginal cleansing with either 1% povidone iodine or chlorhexidine or no toileting (control) during elective CSTo determine the number of post-CS infections among women that will undergo pre-operative vaginal cleansing with 1% povidone iodine or chlorhexidine or no toileting (control) during emergency CSTo compare the rate of infections among the three groups that receive either 1% povidone iodine or chlorhexidine or no toileting for vaginal irrigation prior to any kind of CSTo identify the best antiseptic wash and methods for vaginal irrigation prior to CS for developing a uniform guideline through locally generated evidenceTo determine the factors that may influence the outcomes, such as post-CS infections or related complications

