## Assignment of interventions: allocation

### Sequence generation {16a}

After inclusion in the trial, each prospective CS patient will be assigned either into the intervention (1% povidone iodine or chlorhexidine) or control (no-irrigation) group by using a block randomisation technique. A permuted block of six will be used to randomise the patients. A third party not related to the study will generate the permuted blocks and allocate the treatment in sealed opaque envelopes.

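### Three objectives (infections by arm in elective CS, infections by arm in emergency CS, influencing factors) need analyses that section 20b says are not planned

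*Protocol article*

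**What the plan says.** The Objectives section lists five aims. The first is to determine how many infections occur "among women that will undergo pre-operative vaginal cleansing with either 1% povidone iodine or chlorhexidine or no toileting (control) during elective" CS, and the second repeats this for emergency CS. The third compares the three arms over any kind of CS. The fifth is to determine what factors may influence the outcomes.

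The statistical methods section {20a} offers three things:
- a summary by arm: "Summary statistics will be presented for all three groups’ infection information";
- an overall comparison: "Primary and secondary outcomes will be compared using ANOVA";
- at the analysts' discretion, a model of each antiseptic against control: "logistic regression analyses will be used to compare the outcomes separately for interventions versus the control group".

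No split by CS type, covariate or factor model is named. Section {20b}, whose heading gives subgroup analyses as its example, then states: "No additional analyses are planned".

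On allocation, section {16a} says "A permuted block of six will be used to randomise the patients" and names no stratification factor. The background reports that "higher rates of infection have been identified in women with ruptured membranes and in women who undergo a CS in labour".

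**The concern.** Two sections of one document pull in opposite directions. An analyst who follows 20b leaves the first, second and fifth objectives unanswered. An analyst who follows the objectives goes against 20b, and the results by CS type or by risk factor will then look post hoc although they were declared aims.

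There is a smaller, related point. The protocol itself treats CS in labour as a risk factor. Emergency CS is an imperfect proxy for that, and its status is settled before the envelope is opened (section {16c}). Yet the comparison of arms takes no account of it. In a trial with few events, a baseline predictor that the objectives already call for is left unused.

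**Working it through.** **1. Objectives against analyses**

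| Objective | What it needs | What {20a} provides | What {20b} adds |
|---|---|---|---|
| 1. Infections by arm, elective CS | Counts by arm within elective CS | Summary by arm only | Nothing |
| 2. Infections by arm, emergency CS | Counts by arm within emergency CS | Summary by arm only | Nothing |
| 3. Comparison of arms, any CS | Comparison of three arms | ANOVA; logistic regression v control | – |
| 5. Influencing factors | A factor table or model | Logistic regression, worded for arm v control only | Nothing |

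**2. The protocol's own sample size figure**

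ES = 0.04/√(0.08 × 0.92) = 0.1474, and ((1.96 + 0.84)/0.1474)² = 360.6, rounded up to 361. This reproduces. The recruitment target of 396 equals 360 × 1.10, or 132 per arm. Whether this formula suits a three-arm comparison is a separate question.

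**3. Expected events**

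Evaluable women per arm: 396 × 0.90/3 = 118.8, about 119. At 8% (control) and 4% (each antiseptic):

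119 × 0.08 + 2 × (119 × 0.04) = 9.5 + 4.8 + 4.8, about 19 infections.

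The 8% comes from overall post-CS infection, whereas the primary outcome is endometritis alone. If endometritis is rarer, there are fewer events.

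**4. What a CS-type stratum would hold**

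The elective/emergency split is not given, so the share is an assumption. This uses 120 evaluable women per arm (361/3, rounded), the same 8/4/4% rates in each stratum and a two-sided 5% level:

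| Share of women in stratum | Women per arm | Infections, three arms | Power, one antiseptic v control |
|---|---|---|---|
| 30% | 36 | 5.8 | 11% |
| 50% | 60 | 9.6 | 15% |
| 70% | 84 | 13.4 | 19% |

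An interaction test, which contrasts two such strata, would also have very low power.

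**5. Events per candidate factor**

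Section {18a} names eight items: membrane rupture duration, labour duration, BMI, gestational diabetes, surgery duration, blood loss, previous CS and vaginal examination at CS. 19/8 is about 2.4 events per factor, too few for an ordinary multivariable logistic model.

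**6. What chance imbalance in CS type could do**

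Assumptions: half of the women have emergency CS; risk is 12% in emergency and 4% in elective CS (mean 8%); the 8-point gap applies in both arms compared.

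- SD of the between-arm difference in emergency share: √(2 × 0.25/119) = 6.5 points; 95% range ±12.7 points.
- Shift in the rate difference at one SD: 6.5 × 0.08 = 0.5 point.
- Shift at the 95% extreme: 12.7 × 0.08 = 1.0 point.
- SE of the rate difference at 8% v 4%: √((0.08 × 0.92 + 0.04 × 0.96)/119) = √(0.112/119) = 3.07 points.
- Ratios: 1.0/3.07 is about one third of an SE; (0.52/3.07)² is about 3% of the sampling variance.

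Range: with a 30% or 70% emergency share, the SD is √(2 × 0.21/119) = 5.9 points, so the shifts are 0.5 and 0.9 point. With a 4-point risk gap (10% v 6%) and a half share they are 0.3 and 0.5 point; with a 12-point gap (14% v 2%), 0.8 and 1.5 points. Every case stays at or below about half an SE.

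**The case against.** **Counts are enough.** The first two objectives ask only for a number of infections, so a table by arm and CS type would satisfy them without subgroup inference. This stands, and it lowers the demand. It does not remove the conflict, because the only summary planned is by arm.

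**Logistic regression could serve the factor objective.** The factors are to be collected, and logistic regression is available where appropriate. As worded, however, it compares interventions with control, and 20b closes the door on anything further.

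**An unseen SAP may cover this.** It could add detail where the protocol is silent. Here the protocol makes a statement, and a SAP cannot honour both the objectives and 20b. The choice of covariate is different: an article often leaves that to the SAP, so the adjustment proposed here is a recommendation and not a correction of an error.

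**Randomisation.** A reader might infer that the unstratified list is a flaw, or that imbalance in CS type could create or hide the treatment effect. The document does not support either. Permuted blocks of six are a valid method, and ordinary chance imbalance is already allowed for in the test and the confidence interval. The 1.0-point shift is the 95% extreme under assumed inputs and only about a third of an SE. Setting it against the planned 4-point effect makes it look larger than it is.

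**Proxy.** The background names labour and ruptured membranes, not emergency CS as such. This stands: CS type captures that risk imperfectly.

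**Conclusion.** The contradiction is on the page and should be resolved. Objectives 1, 2 and 5 call for analyses that 20a does not supply and 20b says are not planned. That conclusion rests on the text alone and needs no assumption. It touches secondary, descriptive aims; the main comparison of arms (objective 3) has a stated analysis.

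The expected yield limits what the missing analyses can be: about 19 events overall, on the protocol's own rates and dropout, and roughly 6 to 13 in a stratum holding 30% to 70% of women. They can be descriptive or exploratory, not confirmatory.

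Adjusting the primary comparison for CS type is worth doing for modest precision and protection against chance imbalance. Its size (0.5 point at one SD and 1.0 point at the extreme, against an SE of 3.1) depends on the assumed emergency share and risks, none of which the protocol gives.

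**What to change.** 1. **Replace the text of 20b.** For example: infection counts, rates and risk ratios with 95% confidence intervals will be reported by arm within elective and within emergency CS, as a pre-specified exploratory analysis, described as descriptive because few events are expected. A treatment-by-CS-type interaction test is optional; if included, its very low power should be stated.
2. **Narrow the fifth objective** to a descriptive table or a penalised exploratory model of the factors collected under {18a}. Surgery duration and blood loss arise after allocation, so their associations should be read descriptively.
3. **Use CS type in the primary comparison**, either as the single covariate or through a Mantel-Haenszel risk ratio stratified by CS type.
4. **Alternatively**, drop objectives 1, 2 and 5 and leave 20b as it is. That is also consistent.

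Stratifying the randomisation list is not proposed: recruitment was to run from September 2020 to December 2021, so it is no longer practical.

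The cost is a few lines of text. One check is needed: {18a} mentions elective or emergency nature only for previous CS, so confirm that the type of the current CS is recorded in the questionnaire or can be taken from the hospital record.
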